## Abstract

**Background:**

The widespread use of chest computed tomography (CT) screening has led to more frequent detection of pure ground-glass nodules (pGGNs). A subset of pGGNs carries a potential risk of malignant transformation. However, the current management strategy for stable pGGNs predominantly involves surveillance, with a notable absence of effective intervention strategies. Traditional Chinese medicine (TCM), as an adjunctive therapy, offers considerable promise. Preclinical studies indicate that Chuanjie Granules (CJG), a TCM compound formulation, may have potential benefits in reducing the size of pGGNs. However, there is a lack of strong evidence from large-scale randomized controlled trials. Consequently, this study aims to evaluate the clinical effectiveness and safety of CJG for pGGNs through a well-designed clinical trial and explore its mechanisms of action.

**Methods:**

This study is a prospective, randomized, triple-blind, placebo-controlled, multicenter clinical trial designed to enroll 172 patients who have been radiologically diagnosed with pGGNs. Participants will be randomly allocated in a 1:1 ratio to receive either CJG or placebo, both with standard health education. The intervention lasts 3 months with participants receiving either CJG or a placebo, followed by a 1-year observational period after treatment. The primary outcome is the change in pGGN maximum diameter, while secondary outcomes include nodule reduction rate, density changes, malignancy risk, and patient-reported outcomes. The study will also use 16S rRNA gene sequencing and gas chromatography–mass spectrometry-based metabolomics to examine oral and gut microbiota and explore microbial-metabolic mechanisms.

**Discussion:**

This study aims to rigorously assess the efficacy and safety of CJG and explore its mechanism of action in the intervention of pGGNs through a randomized controlled trial. Positive outcomes are anticipated to furnish the first high-quality evidence-based medical support for the use of TCM in the early intervention of pGGNs, thereby potentially enhancing clinical decision-making processes.

**Clinical trial registration:**

http://itmctr.ccebtcm.org.cn/, identifier ITMCTR2025001413.

## Introduction

1

The extensive utilization of multi-slice spiral computed tomography (CT) for the early detection of lung cancer has significantly increased the identification of individuals presenting with pulmonary nodules (1). Among these, pure ground-glass nodules (pGGNs) are frequently observed radiological findings, with potential etiologies including inflammation, hemorrhage, atypical adenomatous hyperplasia (AAH), and early-stage lung cancers such as adenocarcinoma *in situ* (2). While the majority of pGGNs are benign, a subset poses a risk of malignant transformation. Current data, though incomplete, suggest that 18 to 53% of resected pGGNs are pathologically diagnosed as invasive adenocarcinoma (IA) (3, 4), with a 5-year recurrence-free survival rate ranging from 22.0 to 94.4% (5, 6). Given the indolent biological behavior characteristic of pGGNs, current guidelines primarily recommend annual low-dose computed tomography (LDCT) surveillance (7–9). However, reports suggest that over 50% of pGGNs exhibit progression during follow-up, representing a significant risk for transition from an indolent phase to a growth phase within the lung adenocarcinoma spectrum (10). Therefore, timely and effective intervention during the early stages of pGGNs is clinically warranted. Presently, Western medical management for stable small nodules predominantly relies on active surveillance, which is marked by a lack of effective therapeutic interventions. Surgical resection or chemoradiotherapy is generally reserved for lesions that are confirmed to be malignant or progressive, both of which are associated with significant invasiveness and considerable adverse effects.

Traditional Chinese Medicine (TCM) presents potential clinical benefits for the “preventive treatment” (zhi wei bing) of pulmonary nodules and early-stage lung cancer. The prolonged surveillance period during follow-up observation provides an ideal opportunity for TCM intervention, which may contribute to the reduction of nodule volume, prevention of malignant transformation, and alleviation of clinical symptoms (11–13). Chuanjie Granules (CJG), a TCM compound granule formulation developed by our research team, is based on extensive clinical experience in the treatment of pulmonary nodules. This formulation consists of seven herbal components: *Vaccaria segetalis, Platycodon grandiflorus, Achyranthes bidentata, Citrus aurantium, Trichosanthes kirilowii, Curcuma longa,* and *Pumex*. The formulation has been submitted for a Chinese invention patent (application no. 202510241770.3). An initial investigation involving 91 patients indicated that CJG significantly decreased nodule size, with a total effective rate of 52.2% (*p* < 0.05) specifically concerning the reduction in diameter of pGGNs (14). Moreover, CJG was well-tolerated and proved effective in enhancing patient quality of life while mitigating symptoms of anxiety and depression. Nonetheless, the study’s findings were constrained by its single-center design, limited sample size, and absence of a placebo control.

To address this, we will conduct a high-quality, randomized, triple-blind, placebo-controlled, multicenter trial to assess the efficacy and safety of CJG. Additionally, we aim to explore its mechanism, hypothesizing its therapeutic effects may involve modulation of the host microbiota and consequent alterations in metabolite profiles. In pursuit of this objective, the study will incorporate 16S rRNA gene sequencing for the analysis of oral and gut microbiota, alongside untargeted metabolomic profiling of saliva and stool samples using gas chromatography–mass spectrometry (GC-MS).

## Materials and methods

2

### Trial design

2.1

This prospective, randomized, triple-blind, placebo-controlled, multicenter clinical trial is designed to enroll 172 patients diagnosed with pGGNs. Participants will be randomly assigned in a 1:1 ratio to either the intervention group, receiving CJG, or the control group, receiving a placebo for CJG, utilizing stratified block randomization. Both cohorts will receive standardized health education and participate in a 3-month intervention with either CJG or a placebo, followed by a 1-year observational follow-up without the study drug. The study flowchart is depicted in Figure 1, while Figure 2 outlines the timeline for enrollment, intervention, and follow-up. The trial protocol is in compliance with the Consolidated Standards of Reporting Trials (CONSORT) guidelines for interventional studies.

**Figure 1 fig1:**
[figure not shown]
Study flowchart. pGGN: pure ground-glass nodule: TCM: Traditional Chinese Medicine: BAI: Beck Anxiety Inventory: BDI-II: Beck Depression Inventory-II; SF-36: 36-item short form health survey: T0: day-7 to day 0: T1: 1 month treatment: T2: 2 months treatment; T3: 3 months treatment; T4: 1 year after end of treatment.

**Figure 2 fig2:**
[figure not shown]
Enrollment, intervention, and follow-up flow chart.

### Participant recruitment

2.2

Participant recruitment for this study will be executed concurrently across three centers: Hospital of Chengdu University of Traditional Chinese Medicine, Sichuan Cancer Hospital, and Chengdu Integrated Traditional Chinese and Western Medicine Hospital. Recruitment methodologies will encompass identification during follow-up appointments at specialized or disease-specific clinics, the placement of recruitment posters within hospital premises, and the utilization of social media campaigns. At each site, qualified research coordinators will conduct preliminary pre-screening of potential participants who express interest, assessing initial eligibility. Subsequently, formal eligibility will be evaluated and confirmed by the attending physician. Eligible participants will then be provided with a comprehensive explanation of the trial procedures, including the treatment regimen, by the investigator. All inquiries and concerns raised by participants will be thoroughly addressed. Following this, written informed consent will be obtained to formally enroll participants in the trial.

### Inclusion criteria

2.3

An imaging report from the past 3 months identifies a pGGN as the largest pulmonary nodule, deemed appropriate for active surveillance rather than surgical intervention, following a multidisciplinary consultation;Aged 18–75 years, irrespective of sex;Voluntarily providing written informed consent.

### Exclusion criteria

2.4

Existing cancer or major organ disease;Current respiratory infection;The use of antibiotics, hormonal therapies, immunosuppressants, or Chinese herbal medications within the preceding 3 months;Taking yogurt or probiotics for nearly a week;Psychiatric or cognitive issues hindering study compliance;The state of pregnancy or lactation;A known hypersensitivity to any component of the study product;Concurrent participation in another clinical trial within the preceding month.

### Withdrawal criteria

2.5

The occurrence of a serious adverse event (SAE) in which continued participation presents a greater risk than benefit;Inadequate compliance, characterized by a failure to adhere to the prescribed medication regimen or the utilization of additional non-protocol therapies for pulmonary nodules;Loss to follow-up during the study period or voluntary withdrawal for any reason.

Upon cessation of treatment or withdrawal from the study, participants will transition into a follow-up phase. The long-term efficacy concerning pulmonary nodules will be evaluated through chest CT findings at the one-year follow-up. Notably, participants whose nodules demonstrate growth meeting established criteria for surgical intervention or who receive a confirmed cancer diagnosis requiring anti-cancer therapy upon completion of the 3-months treatment course will be discontinued from further efficacy follow-up.

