#### Primary outcome

2.7.1

The primary outcome, the change in the maximum diameter (ΔD) of the pGGN from baseline, which will be calculated using the following formula:

ΔD=Bmax−Pmax

Where: *Bmax* = baseline maximum diameter and *Pmax* = post-treatment maximum diameter.

Measurements will adhere to the 2017 Fleischner Society guidelines for pulmonary nodule assessment (16). For participants with multiple nodules, the maximum diameter of the nodule with the highest risk or the largest size will be measured. In cases where multiple nodules share an identical maximum diameter, the nodule will be selected for measurement following risk stratification, prioritizing the highest-risk nodule. The analysis of CT images will be conducted by two independent board-certified radiologists, each possessing relevant clinical expertise. Using lung window settings (window width: 1400 HU; window level: −700 HU), the pGGN will be identified, and its maximum diameter will be measured on the transverse slice where it appears largest. Triplicate measurements will be conducted for each nodule at each time point, and the average value will be calculated and recorded in millimeters (mm), rounded to the nearest integer. Assessments will be performed at baseline, at 3 months (end of treatment), and at 1 year (end of follow-up).

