### Statistical analysis

2.14

Data analysis will be conducted utilizing IBM SPSS Statistics version 28.0 (IBM Corp., Armonk, NY, United States). Efficacy analyses will encompass all patients who are randomly assigned (full analysis set, FAS; adhering to modified intention-to-treat principles) as well as all patients who completed the trial protocol (per-protocol set, PPS). Any discrepancies between the FAS and PPS analyses will be evaluated from both clinical and statistical standpoints. The safety analyses will be based on the safety set (SS), which includes all patients who received at least one dose of the investigational drug. All hypothesis tests will be two-tailed, with a significance threshold set at *α* = 0.05. *p*-values will be calculated from the relevant statistical tests, with *p* ≤ 0.05 being regarded as statistically significant.

To conduct a longitudinal comparison of the trajectories of changes in the maximum diameter of pGGN relative to baseline across various groups at follow-up time points, a linear mixed model will be utilized. This model will incorporate random subject intercepts to account for within-subject correlations arising from repeated measurements. The fixed effects will include group, follow-up time points, and their interaction, while covariates will consist of age and baseline pGGN maximum diameter. For other continuous variables, intergroup comparisons will be performed using independent samples t-tests for normally distributed data or Mann–Whitney U tests for non-normally distributed data, contingent upon the results of normality tests. Categorical variables will be compared using chi-square tests or Fisher’s exact tests. To assess the potential impact of distinct clinical characteristics on treatment efficacy, predefined subgroup analyses will be conducted, considering factors such as gender, age, smoking status, number of lung nodules, and risk stratification. Interaction tests will be performed to investigate whether differences in efficacy between groups vary across these subgroup factors.

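### Efficacy follow-up ends for participants who progress to surgical criteria or confirmed cancer at month 3, and nothing counts these events in the 1-year outcomes

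*Protocol article*

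**What the plan says.** Withdrawal criteria sets a general rule and an exception. The general rule: "Upon cessation of treatment or withdrawal from the study, participants will transition into a follow-up phase". The purpose is also given: "The long-term efficacy concerning pulmonary nodules will be evaluated through chest CT findings at the one-year follow-up". The exception covers "participants whose nodules demonstrate growth meeting established criteria for surgical intervention or who receive a confirmed cancer diagnosis" that requires anti-cancer therapy; these people, "upon completion of the 3-months treatment course will be discontinued from further efficacy follow-up".

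The primary outcome is "the change in the maximum diameter (ΔD) of the pGGN from baseline", assessed at 3 months and at 1 year (Primary outcome). Reduction rate with its CR/PR/SD/PD categories, nodule density and Mayo malignancy risk are also assessed at both times (Long-term secondary outcomes). There, PD is a reduction of less than 25% or any increase.

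Statistical analysis gives diameter change a linear mixed model with a random subject intercept, group, time, their interaction, age and baseline diameter. Other continuous outcomes get t or Mann-Whitney tests, and categorical outcomes chi-square or Fisher tests. On analysis sets: "Efficacy analyses will encompass all patients who are randomly assigned (full analysis set, FAS; adhering to modified intention-to-treat principles"), together with "all patients who completed the trial protocol (per-protocol set, PPS").

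No section says that surgery for growth or a cancer diagnosis counts as PD, or as any other efficacy event, at 1 year.

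**The concern.** People who stop treatment or withdraw for other reasons move on to a 1-year CT. The group whose efficacy follow-up the protocol itself ends is the group with the clearest treatment failure, so the missing data depend on the outcome and are imposed by the plan.

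The simple 1-year tests use only people with 1-year values. Someone already in the PD category at month 3 leaves both numerator and denominator of the 1-year response table. If completing the protocol includes the 1-year visit, the per-protocol set has the same gap and cannot serve as a check.

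The Introduction motivates the trial by the risk of malignant transformation, and the Discussion presents the year of monitoring as its evidence on long-term effects. The 1-year result is therefore where the loss matters.

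**Working it through.** **Plan's own figures.** Pilot changes (Sample size calculation) are 1.11 ± 2.12 mm for CJG and 0.19 ± 1.25 mm for control, a difference of 0.92 mm. The averaged-variance SD is √((2.12² + 1.25²)/2) = 1.74. A two-sided t-test at 0.05 with 90% power needs 77 per arm, and 77/0.9 = 85.6, so 86 as stated. The MCID is 0.5 × 1.25 = 0.625, given as 0.63 mm. Neither figure is in question.

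**Assumptions not in the document.** Changes are normal; the true 1-year difference is also 0.92 mm; removal occurs when growth at month 3 exceeds 2 mm (change below −2); the month-3/1-year correlation ρ is 0.6 or 0.8; the 1-year SD is k = 1.0 or 1.5 times the month-3 SD.

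**Completers only.** For an arm with mean m and SD s, let a = (−2 − m)/s. The proportion removed is Φ(a). The mean 1-year change among those left rises by ρ·k·s·λ, where λ = φ(a)/(1 − Φ(a)).

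Pilot SDs:
- CJG: a = (−2 − 1.11)/2.12 = −1.467; removed 7.1%; s·λ = 0.3105
- Control: a = (−2 − 0.19)/1.25 = −1.752; removed 4.0%; s·λ = 0.1119
- Difference = 0.92 + ρk × 0.1986, from 0.92 + 0.6 × 0.1986 = 1.04 to 0.92 + 1.2 × 0.1986 = 1.16 mm

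Equal SDs of 1.25: s·λ is 0.0227 and 0.1119, so the difference is 0.92 − ρk × 0.0892, or 0.87 down to 0.81 mm.

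Equal SDs of 1.74: s·λ is 0.1459 and 0.3509, so the difference is 0.92 − ρk × 0.2050, or 0.80 down to 0.67 mm.

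**Planned mixed model.** Large-sample simulation of a random-intercept model with group-by-time means, keeping every month-3 value; age and baseline diameter were left out for simplicity.

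| SD, CJG / control | Expected removed of 86, CJG / control | Completers, 1 year (mm) | Mixed model, k = 1.0 | Mixed model, k = 1.5 |
|---|---|---|---|---|
| 2.12 / 1.25 | 6.1 / 3.4 | 1.04–1.16 | 0.92 | 1.00–1.02 |
| 1.25 / 1.25 | 0.6 / 3.4 | 0.81–0.87 | 0.92 | 0.88–0.89 |
| 1.74 / 1.74 | 3.2 / 9.0 | 0.67–0.80 | 0.92 | 0.82–0.84 |

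**Removal driven by growth that the month-3 value does not show.** Here removal was made to depend on the 1-year value, with ρ from 0.5 to 0.9, equal SD at both times, and a cutoff removing 2 to 10% of controls. The mixed model gives 0.95–1.09 mm with the pilot SDs and 0.79–0.91 mm with SD 1.25 in both arms. The largest error is 1.09 − 0.92 = 0.17 mm.

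**The case against.** The strongest reply is that diameter, the primary outcome, is not analysed in completers. The mixed model keeps the month-3 value of everyone removed, and recovers 0.92 mm when that scan shows the growth and the SDs at the two times agree. This stands. A reader might infer from the pilot-SD case that the primary 1-year effect would be 13 to 26% too large (1.04/0.92 to 1.16/0.92) and in favour of CJG. The documents do not support that: those figures belong to a completers analysis the plan does not use for diameter, the 2 mm cutoff is assumed, and equal arm SDs reverse the sign.

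Other stronger readings also fail:
- **All surgeries and cancers vanish from the efficacy data.** The exception is worded for the end of the 3-month course and stops only further follow-up. Month-3 growth is measured and classed as PD first. Later events are not clearly covered.
- **The per-protocol set certainly excludes these people.** That is an inference; completion is not tied to the 1-year visit.
- **Early stoppers lack a month-3 CT.** The Primary outcome section schedules that CT without excepting them.
- **The FAS is compromised.** Calling an all-randomised set modified intention-to-treat is loose wording and shows no exclusion of these participants.

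It can also be said that a resected nodule has no 1-year diameter and that handling of such events belongs in the unseen SAP. The first part is true of diameter, but not of response category, where the event itself can be classified. On the second, an SAP can choose a method for missing data, but cannot recover data that sites are told to stop collecting.

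**Conclusion.** The point holds for the 1-year outcomes. As written, the 1-year response, reduction rate, density and Mayo risk comparisons lose participants because of their outcome, and the simple tests named for them give no protection. No error was computed on the scales of those outcomes; the diameter figures only illustrate the mechanism. For diameter, the mixed model is close to unbiased in the favourable case and off by roughly 0.1 to 0.2 mm otherwise, against an MCID of 0.63 mm. The direction depends on the arm SDs and cannot be predicted. All sizes rest on the assumed cutoffs, correlations and SD ratios, and on the pilot difference persisting to 1 year. The 3-month comparison and the sample size are unaffected. This is a cheap improvement to make before follow-up data are lost.

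**What to change.** - Amend Withdrawal criteria so that these participants remain in the FAS efficacy data. Record the event, its date and the last CT before surgery or anti-cancer therapy. State whether the same applies to events later in the follow-up year.
- Count surgery for growth, or confirmed malignancy, as PD in the 1-year response analysis, and tabulate these events by arm.
- Keep the mixed model for diameter, using all CTs up to the event, and add a worst-rank or other not-missing-at-random sensitivity analysis at 1 year. Carrying the last pre-event diameter forward is not a clean substitute as the main analysis: with the pilot SDs and the 2 mm cutoff it gives 0.85 to 0.96 mm, against 0.92 mm.
- Do not make completion of 1-year follow-up a condition of the per-protocol set for these participants.

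The cost is protocol wording, one CRF page and one sensitivity analysis. Only data collection and analysis change; clinical management stays as it is.

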### Interventions

2.6

Eligible participants will be provided with standardized health education concerning the management of pulmonary nodules. This education encompasses advice on fostering a positive mindset, adhering to a balanced diet, ceasing smoking, limiting alcohol consumption, engaging in regular physical activity, and minimizing exposure to smoke, dust, and irritant gases. Additionally, to maintain the integrity of oral and fecal microbiome and metabolomics analyses, participants will be advised to abstain from consuming probiotics (including yogurt, etc.) for one week prior to enrollment and throughout the duration of the interventional treatment period.

Intervention Group: Participants will be administered CJG orally. CJG is formulated from a compound herbal medicine preparation comprising *V. segetalis*, *P. grandiflorus*, *A. bidentata*, *C. aurantium*, *T. kirilowii*, *C. longa*, and *Pumex*, with the specific dosages being proprietary. Initially, active constituents are extracted from these medicinal sources. Subsequently, the extract is concentrated into a viscous paste, which is then combined with appropriate excipients such as starch and dextrin, and dried to yield uniform, easily dissolvable dry granules. These herbs are processed into 6 grams of non-decoction granules (one packet) by Sichuan Neo-Green Pharmaceutical Technology Development Co., Ltd. (Sichuan, China), in compliance with the Production Quality Management Code. Patients are advised to consume a total daily dose of 18 grams, divided into three 6-gram doses to be taken after each meal. Each dose should be dissolved in 100 mL of boiling water, stirred, covered, and allowed to cool to a temperature of 30–37° C before consumption. Throughout the three-month intervention period, the dosage administered to all participants remains constant, irrespective of age, as this formulation constitutes a standardized fixed dose for adults. Previous studies have confirmed the safety and efficacy of this dosage regimen (14). Quality control assessments conducted by the manufacturer verify adherence to the standards specified in the *Chinese Pharmacopoeia (2020 Edition)* (15).

Control Group: Participants in the control group will be administered a matched placebo. This placebo, produced by the same manufacturer, is composed primarily of maltodextrin and food-grade coloring agents. It is designed to be indistinguishable from the CJG in terms of appearance (color and shape), odor, and packaging. The instructions for administration are identical to those provided to the intervention group.

